### CMBs evaluation

3.3

An imaging physician and a neurologist will assess the SWI of the 2 MRIs to evaluate the old CMBs at the time of admission and new CMBs in the acute phase. If the 2 physicians have different opinions on the CMBs judgment, a third senior neurologic physician will intervene until an agreement is reached.

CMBs are examined by SWI. Their diameter are generally less than 5 mm. These small dot-like lesions are thought to be old perivascular collections of hemosiderin deposits. They can be detected by SWI after 48 hours, so SWI examination within 48 hours of stroke onset can identify old CMBs, and SWI at 14 days after onset can identify the new CMBs.

The diagnose of CMBs^[31]^ is as follows:

(1)the low-density signal detected by SWI, round or oval, at least 1/2 of the lesion is surrounded by brain parenchyma, with a clear boundary and a volume of 2 to 10 mm^3^;(2)T1 and T2 sequences usually do not show abnormal signals;(3)rule out the diffuse axonal injury caused by brain trauma;(4)exclude other conditions such as calcification, cavernous hemangioma, and small blood vessel blanking that may show similar signal on SWI.

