### Sample size

2.4

We used EpiCalc 2000 for sample size estimation, set significance = 0.05, power = 80%, ratio of cases to controls = 1, risk ratio to detect = 2, proportion (%) controls exposed = 15% (4.4%–24.5%). The sample size was 207 in each of the observation group and the control group.

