### Brain MRI

3.2

The patients will complete the brain MRI within 48 hours and 14 days after stroke onset. By comparing 2 SWI to evaluate the new CMBs, including whether there are new CMBs, the number of CMBs and the location of CMBs.

The patients will be scanned using a SEIMENS MAGNETOM Avanto 1.5 Tesla scanner. Examinations include SWI, diffusion weighted imaging, T1-weighted imaging, T2-weighted imaging, and fluid attenuation inversion recovery. Diffusion weighted imaging scanning sequence: repetition time = 3400 ms; echo time = 102 ms; flip angle = 90; field of view = 230 × 230 mm; acquisition matrix = 192 × 192 mm; no. of excitations = 1.0; thickness = 6.0 mm; gap = 1.2 mm; scan time = 63 seconds. SWI scanning using a 3 dimension- fast field echo (3D-FFE) sequence as follow: repetition time = 17 ms, echo time = 24 ms, flip angle = 15; field of view = 201 × 230 mm; acquisition matrix = 354 × 512 mm; no. of excitations = 1.0; thickness = 1.0 mm; layer = 100; scan time = 209 seconds.

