### Outcome assessment

3.4

The outcomes will be assessed by independent assessors, who had been trained before participating in this study and blinded to the randomization. All outcome data for participants whether completed or withdrawn during the study will be collected and recorded in the case report form.

Primary outcome: to evaluate the effect of NBP on new CMBs in patients with AIS.

Secondary outcome: to evaluate the effect of NBP on sICH and the National Institute of Health stroke scale score at 14 days of onset.

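### The two size statements for a microbleed do not agree: the diagnostic volume limit excludes round lesions of about 2.7 to 5 mm that the same section describes as microbleeds

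*Protocol article*

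**What the plan says.** Section 3.3 (CMBs evaluation) gives the size of a CMB twice. The descriptive paragraph says: "Their diameter are generally less than 5 mm". The diagnostic list that follows opens with "the low-density signal detected by SWI, round or oval" and adds, as part of the same item, a requirement of "a volume of 2 to 10 mm^3". The section does not say which statement governs, how a volume would be measured, or what becomes of a lesion outside the limits. Two physicians read the scans, and a third, senior one resolves disagreements.

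The definition feeds the primary endpoint directly. Section 3.4 states: "Primary outcome: to evaluate the effect of NBP on new CMBs in patients with AIS". Section 3.2 explains that new lesions are found "By comparing 2 SWI to evaluate the new CMBs", and lists presence, number and location as what is recorded.

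**The concern.** A diameter and a volume describe different scales, and these two limits lie far apart once they are put on the same one. A lesion can be a CMB under the descriptive sentence and not a CMB under the diagnostic item. The sole primary outcome depends on that classification. Two readers working from the same page could classify the same lesion differently, and the third reader has no text with which to settle it.

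The direction matters because this is a safety question. Section 1 chooses new CMBs because they are a more sensitive marker than symptomatic haemorrhage; a narrow size window works against that aim. Section 4 (Discussion) says that finding no effect on new CMBs would confirm the drug's safety. A rule that turns some new bleeds into non-events makes that finding easier to reach.

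**Working it through.** **Inputs.** All sizes come from section 3.3: volume limits of 2 and 10 mm^3, a descriptive diameter limit of 5 mm, and a round or oval shape. The document gives no distribution of lesion sizes.

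**Step 1: volume limits as diameters, for a sphere.** V = πd³/6, so d = (6V/π)^(1/3).
- V = 2 mm^3: d = (12/π)^(1/3) = 3.82^(1/3) = 1.56 mm.
- V = 10 mm^3: d = (60/π)^(1/3) = 19.10^(1/3) = 2.67 mm.

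**Step 2: diameters as volumes.**

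| Diameter (mm) | Volume πd³/6 (mm^3) | Within 2 to 10 mm^3? |
|---|---|---|
| 1.5 | 1.8 | no |
| 2 | 4.2 | yes |
| 2.5 | 8.2 | yes |
| 3 | 14.1 | no |
| 4 | 33.5 | no |
| 5 | 65.4 | no |

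The 10 mm^3 cap is 10/65.4 = 15% of the volume of a 5 mm sphere.

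**Step 3: oval lesions.** For a prolate ellipsoid with long axis L and aspect ratio k, V = πL³/(6k²), so at the cap L = (6 × 10 × k²/π)^(1/3).
- k = 1.5: L = 3.50 mm.
- k = 2: L = 4.24 mm.
- k = 3: L = 5.56 mm.

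Only a clearly elongated lesion comes near 5 mm and still meets the cap.

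**Step 4: share of lesions affected.** The window is 2.67 − 1.56 = 1.11 mm wide, or 1.11/5 = 22% of the 0 to 5 mm diameter scale. That is a share of millimetres, not of lesions. The share of lesions needs an assumed distribution of diameters, truncated to 0 to 5 mm:

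| Assumed diameters (mm) | Kept | Dropped |
|---|---|---|
| Normal, mean 3.5, SD 1 | 19% | 81% |
| Uniform | 22% | 78% |
| Normal, mean 3, SD 1 | 30% | 70% |
| Normal, mean 2.5, SD 0.8 | 47% | 53% |
| Normal, mean 2, SD 0.7 | 57% | 43% |
| Normal, mean 2.1, SD 0.4 | 83% | 17% |

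**Step 5: how power responds to a lower event rate.** Inputs from section 2.4: 207 per group, two-sided 0.05, an effect of 2, and a planning rate given as "proportion (%) controls exposed = 15% (4.4%–24.5%)". The test is Fisher's exact test (section 3.7). The article calls the 2 a risk ratio, but 207 per group is close to what an odds ratio of 2 requires (15% against 26.1%: 208 per group by the usual formula for two proportions, against 121 for 15% versus 30%). Both readings are therefore shown. The rates below 15% are assumptions, not predictions.

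| Control rate | Exact power, risk ratio 2 | Exact power, odds ratio 2 |
|---|---|---|
| 15% | 95% | 77% |
| 12% | 87% | 69% |
| 10% | 79% | 62% |
| 7.5% | 63% | 51% |

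Power falls as events are lost, but the document does not say which row a literal reading would produce.

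**The case against.** Several points on the other side are sound and limit what can be claimed.

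- **Strict contradiction.** A reader might say that the section contradicts itself outright. It does not: 1.56 to 2.67 mm lies inside less than 5 mm, and the diameter sentence is background, hedged by the word generally. What stands is that a description and a criterion have very different upper limits and are not reconciled.
- **Loss of most lesions.** A reader might infer this from the narrow window. The document gives no size distribution, and under the assumptions above the loss is sometimes below one half. Patients also lose event status less readily than lesions are lost: if the outcome is whether a patient has any new CMB, one qualifying lesion is enough.
- **Collapse of power.** It is tempting to drop the control rate to 4.4%, where power for a risk ratio of 2 is 37%. That rate is the lower end of the published incidence quoted in sections 1 and 2.4 and has no link to the size rule. Reaching it from 15% would need 1 − 4.4/15 = 71% of event patients to be lost.
- **A unit slip.** Millimetres written as cubic millimetres is possible but cannot be shown from the document. A range of 2 to 10 mm would still differ from 5 mm at its upper end.
- **Literal use.** Section 3.3 describes visual judgement and no volumetry, so readers may not apply the volume limit strictly. The readers also compare the two scans, so a lesion visible at baseline is unlikely to be called new merely because its size has changed.
- **Larger bleeds.** Symptomatic haemorrhage is a secondary outcome and adverse events are recorded, so part of what the criterion excludes would be captured elsewhere. A larger bleed without symptoms is not explicitly covered.

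None of this removes the defect. If readers ignore the volume limit, the written definition of the primary endpoint is not the one in use; if they apply it, round lesions of 3 to 5 mm are excluded.

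**Conclusion.** The point holds in a limited form. Section 3.3 states two CMB sizes that do not agree. Applied literally, the diagnostic criterion excludes round lesions of about 2.7 to 5 mm and those under about 1.6 mm, which the description in the same section would include. New bleeds can therefore be scored as non-events in the sole primary outcome, and readers can differ on the same lesion. The conversion assumes a sphere; moderately oval lesions raise the upper limit to about 3.5 to 4.2 mm on the long axis.

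The same rule applies in both arms, so the expected consequence is inconsistent reading, fewer counted events and lower power, with a null result correspondingly easier to reach. The document does not support a figure for the lesions, events or power lost. This is an error in a stated rule, not detail that an article leaves to a fuller document.

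**What to change.** Before any scan is read, replace the two statements with one size criterion in one unit. A linear diameter in millimetres suits the visual reading that the section describes. The sponsor should check the limits against the source cited at the diagnostic list (reference 31), which will also show whether the cubic unit is a slip. Apply the same criterion to both scans. State that a new haemorrhagic lesion above the upper limit is recorded as haemorrhage and not as the absence of an event.

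The cost is small: a line or two in section 3.3 and in the reader instructions. If reading has already begun, scans already read should be checked against the reconciled criterion, with the readers unaware of allocation.

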### Outcome assessment

3.4

The outcomes will be assessed by independent assessors, who had been trained before participating in this study and blinded to the randomization. All outcome data for participants whether completed or withdrawn during the study will be collected and recorded in the case report form.

Primary outcome: to evaluate the effect of NBP on new CMBs in patients with AIS.

Secondary outcome: to evaluate the effect of NBP on sICH and the National Institute of Health stroke scale score at 14 days of onset.

### Adverse events

3.5

From the time the patient is enrolled to the last follow-up, any adverse medical events regardless of whether they are causally related to the test drug, will be determined to be adverse events. The researchers will record and report all adverse events. The record includes the occurrence time, severity, duration, measures and outcomes of the adverse events, and separate explanation its potential related drugs.

### Quality control and data collection

3.6

Due to the fact that any nonstandard or bias input of clinical data can dominate the bias of results, 2 researchers will independently gather the data with case report forms. The collected data will be input into a dedicated computer. The above process will maximize the reliability and safety of the all data. In order to guarantee the quality of the study, all researchers will be required to have an official license for at least 2 years of protocol study and clinical experience.

### Data analysis

3.7

Statistical analyses will be conducted with SPSS version 20.0 software (SPSS, Chicago, IL). Statistical differences between the 2 groups will be tested using Student *t* test for normally distributed variables or Fisher exact test for dichotomous variables. Two-tailed *P* values < .05 will be considered statistically significant.

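### The primary comparison is fixed as an unadjusted Fisher exact test although old CMBs are read on every first scan; a model adjusted for baseline CMBs would be more efficient at almost no cost

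*Protocol article*

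**What the plan says.** Section 3.7 (Data analysis) fixes the methods: a Student t "test for normally distributed variables or Fisher exact test for dichotomous variables", with the rule that "Two-tailed *P* values < .05 will be considered statistically significant". It names no covariate and no other test.

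Section 3.2 (Brain MRI) compares the two susceptibility-weighted scans for new CMBs, "including whether there are new CMBs, the number of CMBs and the location of CMBs". Section 3.3 (CMBs evaluation) has two physicians "evaluate the old CMBs at the time of admission and new CMBs in the acute phase", so baseline CMB status is read for every patient scanned.

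Section 3.4 (Outcome assessment) words the primary outcome as an aim, the effect of the drug on new CMBs, without choosing between presence and count. The secondary outcomes are symptomatic intracranial haemorrhage and the "National Institute of Health stroke scale score at 14 days of onset".

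Section 2.4 (Sample size) works with a proportion: "set significance = 0.05, power = 80"%, "ratio of cases to controls = 1", "risk ratio to detect = 2", 15% in controls, giving 207 per arm.

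**The concern.** There are two mismatches. First, the sample size rests on a calculation for an uncorrected comparison of two proportions, while the analysis uses Fisher's test, which is conservative at this size. The named test therefore falls short of the planned power at the effect that yields 207. Second, the trial reads a plausible predictor of the outcome in every patient and does not use it in the comparison.

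This matters because the Discussion says that a finding of no effect on new CMBs would confirm the drug's safety. In a trial read that way, avoidable loss of power makes false reassurance more likely, and a P value alone does not show how much harm the data still allow.

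**Working it through.** **Inputs from the article.** Two-sided alpha 0.05, power 80%, allocation 1:1, control proportion p0 = 0.15, effect 2 (labelled a risk ratio), n = 207 per arm.

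**Step 1: reproduce 207.** Pooled formula without continuity correction:

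n = [1.960·√(2p̄(1−p̄)) + 0.842·√(p0(1−p0) + p1(1−p1))]² / (p1−p0)²

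- *Effect read as an odds ratio of 2:* p1 = 2(0.15)/(1 + 0.15) = 0.2609 and p̄ = 0.2054. The first term is 1.960 × √0.3265 = 1.120. The second is 0.842 × √(0.1275 + 0.1928) = 0.476. Then n = 1.596²/0.1109² ≈ 207.3, or 208 rounded up. This matches 207. With a continuity correction it is 225.
- *Effect read as a risk ratio of 2:* p1 = 0.30 gives 121, or 134 with correction. Neither matches.
- One-sided versions give 164 or 181 (odds ratio) and 95 or 108 (risk ratio). None matches.

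So 207 corresponds to 15% against 26.1% with an uncorrected two-sided test.

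**Step 2: power of the unadjusted tests at 207 per arm.** Every pair of binomial counts was enumerated, and the probabilities of the pairs that reject at two-sided 0.05 were summed.

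| Control vs NBP | Fisher | Uncorrected chi-square |
|---|---|---|
| 15% vs 15% (true type I error) | 3.6% | 4.9% |
| 15% vs 26.1% | 76.9% | 80.2% |
| 15% vs 30% | 94.8% | 95.9% |

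At the effect behind 207, Fisher costs 80.2 − 76.9 = 3.3 points.

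**Step 3: adjustment for baseline CMBs.** The article does not say how common old CMBs are or how strongly they predict new ones. *Assumptions:* prevalence 30%, and odds ratios of 1 to 8 for new CMBs given old CMBs. The overall proportions were held at 15% and 26.1%. There were 4,000 simulated trials per setting (Monte Carlo standard error √(0.8×0.2/4000) ≈ 0.6 points). The adjusted analysis is logistic regression on treatment and baseline CMB presence.

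| Assumed odds ratio, old → new CMBs | Fisher | Chi-square | Adjusted logistic |
|---|---|---|---|
| 1 | 77.2% | 80.5% | 80.3% |
| 2 | 76.5% | 79.8% | 80.4% |
| 3 | 77.4% | 81.0% | 82.6% |
| 5 | 77.5% | 80.7% | 84.3% |
| 8 | 76.4% | 79.8% | 86.5% |

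A separate run of 1,500 trials using the likelihood-ratio test gave 87.3% at an odds ratio of 8. Of the total gain over Fisher (about 3 to 10 points), about 3 come from leaving Fisher and about 0 to 7 from the adjustment itself.

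**Step 4: other outcomes.** With 15% of controls expected to have any new CMB, the count is zero in about 85% of them and cannot be normally distributed. The day-14 stroke scale score is ordinal and usually skewed. Section 3.7 limits the t test to normal variables, so neither outcome has a suitable named test.

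**The case against.** The strongest reply is that the document is a journal article, and covariate models or methods for counts and ordinal scores are usually left to an analysis plan that is not shown. That stands for the count, ordinal and death-ranking models, whose absence is no finding. It does not cover the primary comparison, because section 3.7 states which test a dichotomous outcome receives.

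Several stronger readings are tempting, and the document does not support them.

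- *The baseline CMB data are thrown away.* They are not: the first scan defines which CMBs are new. They are only unused as a covariate.
- *The trial is underpowered.* At the effect as labelled, a risk ratio of 2, Fisher has 94.8% power. The 3-point shortfall exists only at the odds ratio of 2 that reproduces 207, and an uncorrected chi-square alone removes it.
- *Fisher is invalid, or chance imbalance could decide the result.* Under randomisation the unadjusted test's error rate already allows for imbalance.
- *Presence, number and location are three primary tests, with a false-positive risk of 1 − 0.95³ = 14%.* That figure needs independent tests, but a count above zero implies presence, and location exists only where there is a lesion. Nor does any section say that each is tested at 0.05: section 3.2 describes image reading and section 2.4 sizes on a proportion.
- *The t test would give false results on CMB counts.* In a null simulation with assumed geometric counts it rejected 5.5% of the time, close to nominal. The case against it is poor fit to the data.

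Two cautions about adjustment also stand. The first scan may be taken up to 48 hours after onset, while the first dose is due within 6 hours, so that scan may follow the start of treatment. The article also does not show that reperfusion treatment precedes randomisation, or that an admission stroke scale score is recorded.

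**Conclusion.** The point holds as one of efficiency. The stated primary test is valid but conservative (true type I error 3.6%), and at the effect that yields 207 per arm it has 76.9% power against the planned 80%. That shortfall needs no outside assumption beyond reading the effect as an odds ratio of 2. Adjusting for baseline CMB presence brings power to about 80% to 87%. The part above 80% rests on the assumed 30% prevalence and on a predictive odds ratio that the article does not give; with a weak predictor it is close to nil. At 15% against 30% there is little left to gain.

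The primary measure should also be fixed in words, since only the sample-size section shows that it is a proportion.

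**What to change.** Before unblinding, amend sections 3.4 and 3.7 as follows.

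- **Primary measure:** the proportion of patients with at least one new CMB at day 14, as the single primary comparison. This is the quantity the sample size uses.
- **Primary analysis:** logistic regression on treatment and baseline CMB presence. Report the adjusted odds ratio together with the standardised risk difference and risk ratio, each with a 95% confidence interval. Keep Fisher as a sensitivity analysis.
- **Status of the first scan:** state that using it as baseline relies on section 3.3, which holds that a scan within 48 hours shows only old CMBs, because it may follow the first dose.
- **Further covariates:** add reperfusion treatment or admission stroke scale score only if recorded before randomisation.
- **Other outcomes:** treat number and location of CMBs as secondary, and do not use the t test for CMB counts or the day-14 stroke scale score.

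The cost is wording and a little more analysis work. No extra patients or scans are needed.

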## Discussion

4

NBP is a neuroprotective drug extracted from celery seeds. Its active ingredient is dl-3-NBP, which can increase the levels of nitric oxide and prostacyclin in the brain vascular endothelium, reduce the intracellular calcium ion concentration, inhibit glutamate release, reduce the content of arachidonic acid, inhibit oxygen free radicals, increase the activity of antioxidant enzymes and other mechanisms for multiple pathological links of cerebral ischemic. Ischemic stroke will develop neurological deficits in the acute phase. Neuroprotective drugs can reduce ischemic injury through various ways and improve the functional prognosis of patients. It can be used as an effective auxiliary method for the treatment of patients with ischemic stroke during the acute phase. Our study will evaluate the safety of NBP in AIS patients. If the research proves that NBP can reduce the new CMBs of AIS, it will provide new evidence for the treatment of NBP in AIS; if the research finds that NBP will not affect the new CMBs, it will confirm the safety of NBP; and if the study finds that NBP will increase the new CMBs, it will remind clinicians to carefully evaluate treatment options for patients at greater risk of bleeding.

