### Study design

2.1

This is a study protocol for a prospective randomized controlled trail that follows SPIRIT 2013 statement: defining standard protocol items for clinical trials and CONSORT 2010 Statement: updated guidelines for reporting parallel group randomized trials.^[27,28]^

This study will be conducted at the Jingjiang People's Hospital and use new CMBs as indicators to evaluate the safety of NBP in patients with AIS. We will enroll patients with AIS and randomly divided them into the control group and the observation group. The control group will be treated according to the guidelines for AIS and the observation group will be given additional NBP. Patients will complete the brain magnetic resonance imaging (MRI) within 48 hours and 14 days after stroke onset to observe the new CMBs through SWI, and evaluate whether the use of NBP will affect the new CMBs in AIS patients (Figs. 1 and 2). Each participant will be required to sign an informed consent form before enrollment. In addition, they all have the right to withdraw from the study at any time.

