### Eligibility criteria

2.7

The inclusion criteria are as follows:

(1)aged ≥18 years;(2)admitted to hospital within 24 hours after stroke onset;(3)hospitalized with the primary diagnosis of AIS and confirmed by brain CT or MRI and(4)the patient or their close family member sign an informed consent form.

The exclusion criteria are as follows:

(1)the modified Rankin Scale score >1 before the stroke;(2)transient ischaemic attack or subarachnoid hemorrhage;(3)treated with drugs containing NBP before enrollment;(4)history of coagulopathy, systemic bleeding, thrombocytopenia, or neutropenia;(5)history of chronic liver disease, liver and kidney dysfunction, increased alanine aminotransferase (more than 3 times the upper limit of normal value), or increased blood creatinine (more than 2 times the upper limit of normal value);(6)unable to cooperate with 2 MRI examinations;(7)history of severe cardiopulmonary disease, bradycardia (heart rate below 60 beats/min) or sick sinus syndrome;(8)life expectancy is less than 14 days or cannot complete the study due to other reasons;(9)allergic to the drug ingredients in this study; and(10)other unsuitable situations.

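### The Discussion reads a null result on new CMBs as confirming the safety of NBP, a broader conclusion than a 14-day imaging surrogate for intracranial bleeding can carry

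*Protocol article*

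**What the plan says.** The Study design section (2.1) says that the trial will "use new CMBs as indicators to evaluate the safety of NBP in patients with AIS". The outcome section (3.4) then sets the "Primary outcome: to evaluate the effect of NBP on new CMBs in patients with AIS". The Discussion (section 4) lays out how three possible results will be read: fewer new CMBs on NBP, no effect, or more. All three readings turn on new CMBs only, and the middle one is that "if the research finds that NBP will not affect the new CMBs, it will confirm the safety of NBP". The Result paragraph of the Abstract describes the expected output in the same general terms, as an assessment of NBP's safety that will inform clinical use.

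Other harms are not absent from the protocol. Section 3.4 continues: "Secondary outcome: to evaluate the effect of NBP on sICH and the National Institute of Health stroke scale score at 14 days of onset". Section 3.5 defines adverse events broadly, whatever their cause and for the whole of follow-up, and adds: "The researchers will record and report all adverse events". Nothing in the article links either source to the safety conclusion.

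**The concern.** The Introduction justifies new CMBs on one ground: sICH is too rare to be a sensitive endpoint, CMBs are a risk factor for it, and new CMBs are more frequent. At most, that supports an inference about the tendency to bleed inside the skull. It does not reach other harms, and it does not replace the clinical event itself when that event is also being counted. The step from no effect on new CMBs to confirmed safety of NBP therefore claims more than the endpoint can show.

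This would remain true if the CMB comparison were perfectly precise and the rates were identical. It is a separate matter from whether a non-significant CMB difference may be read as no effect, and adding an equivalence margin for CMBs would not cure it. What is at stake is the message to clinicians, whom the Abstract names as the users of the result.

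**Working it through.** **1. What the trial is sized for.** Section 2.4 uses "set significance = 0.05, power = 80"%, 1:1 allocation, a control rate of 15% and a ratio of 2, and gives 207 per group. The check uses the usual two-proportion formula, two-sided, without continuity correction:

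n = [1.96·√(2·p̄(1−p̄)) + 0.84·√(p0(1−p0) + p1(1−p1))]² / (p1−p0)², with p̄ = (p0+p1)/2.

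- Ratio read as an odds ratio: p1 = 2×0.15/(1+0.15) = 0.261, so n = 207.3 (208 rounded up). This reproduces the stated figure.
- Ratio read as a risk ratio: p1 = 0.30, so n = 121. This does not reproduce it.

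The labelling is a separate matter. For this point, the sample size was set by new CMBs and by no other harm.

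**2. Does the stated reading depend on anything else?**

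| Section | What it fixes | Tied to the safety conclusion? |
|---|---|---|
| 2.1 | New CMBs are the safety indicator | Yes |
| 3.4, primary | New CMBs | Yes, through the Discussion |
| 3.4, secondary | sICH and the stroke scale score at 14 days | No |
| 3.5 | All adverse events recorded and reported | No |
| 4 | No effect on new CMBs means safety is confirmed | States the conclusion |

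**3. An illustration (invented counts, not a forecast).** Take 31/207 (15.0%) with new CMBs in both arms: Fisher P = 1.0, so the middle reading applies. Now suppose 8/207 versus 1/207 sICH. The test in section 3.7 gives P of about 0.037. The difference is 7/207 = 3.4 percentage points. Its simple standard error is √(0.0386×0.9614/207 + 0.0048×0.9952/207) = 0.0142, so the 95% interval is about 0.6 to 6.2 points. The trial would hold evidence of clinical harm while the condition for confirmed safety was met.

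**4. Would a significance test on the other harms be enough?** No. At 207 per group:

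- The Introduction cites serious intracranial haemorrhage of 0.9% versus 0.4% from an antiplatelet study. Borrowed here as an assumption, these rates imply 207×0.009 = 1.9 and 207×0.004 = 0.8 expected events. Power is about 9% by normal approximation and about 0.5% by exact enumeration of Fisher's test. Power of 80% would need about 4,054 per group.
- For a doubling of an assumed control rate, Fisher power is as follows.

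| Assumed control rate | Power |
|---|---|
| 1% | about 5% |
| 2% | about 14% |
| 3% | about 24% |
| 5% | about 42% |

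- With no events on placebo, at least 6 on NBP are needed for P < .05; with 1 on placebo, at least 8.

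A non-significant difference in such events would thus be the expected result even under a real doubling. Intervals are needed, not P values alone.

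**5. Precision of the CMB result itself.** Equal rates of 31/207 give a standard error of the log risk ratio of √(2×(1/31 − 1/207)) = 0.234. The 95% interval for the risk ratio is exp(±1.96×0.234), about 0.63 to 1.58. Even for new CMBs, identical observed rates would leave a 50% relative increase inside the interval.

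**The case against.** The strongest reply is that the sentence is narrative in a Discussion, outside both the outcome and the data analysis sections. It describes what three primary results would suggest and does not set a rule that overrides other evidence. This stands. A reader might infer that NBP would be declared safe despite an excess of sICH, death, or hepatic or cardiac events. The documents do not support that: sICH is a named secondary outcome, section 3.7 supplies a test for it, and all adverse events are to be reported. In the illustration above, the 8 versus 1 split would itself be reported as significant. To say that it would be set aside is to attribute an intention found nowhere in the text.

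Context also narrows the word safety. The Introduction speaks mainly of bleeding risk, and the Background and Conclusion of the Abstract already confine the aim to new CMBs. That softens the point but does not remove it: sections 2.1 and 4 and the Abstract's Result use the unrestricted word, and even a claim about bleeding safety would need sICH beside the imaging result.

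A reader might also infer from exclusions such as "history of severe cardiopulmonary disease, bradycardia (heart rate below 60 beats/min) or sick sinus syndrome" that these were suspected harms of NBP. The eligibility section gives no reason for them, so the inference is not made here. Nor is the absence of a detailed list of safety endpoints a defect, since a condensed article may leave that to the full protocol or analysis plan.

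**Conclusion.** The point holds as a fault of scope in the planned interpretation. A finding of no effect on new CMBs would support a statement about new CMBs in the patients enrolled. It cannot confirm the safety of NBP, and the stated reading gives no role to sICH or adverse events, although both are collected.

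The fault concerns what may be concluded; no planned test or sample size is invalidated. No single number measures it. The calculations show only that a contradictory sICH result is compatible with the wording and that rare harms are poorly resolved at 207 per arm: about 5% to 42% power for a doubling from assumed control rates of 1% to 5%. Those rates and the 8 versus 1 split are assumptions. The conclusion itself rests on the text and does not depend on them.

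**What to change.** - In the Discussion, in section 2.1 and in the Result paragraph of the Abstract, limit the conclusion from the primary outcome to the effect of NBP on new CMBs in the enrolled population.
- Make any broader safety statement only alongside sICH, deaths and adverse events. Compare each by arm as a difference with a 95% confidence interval, using a method suited to small counts (a score interval, for example).
- State that a non-significant difference in these rare events will not be read as evidence of safety.

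The cost is a narrower headline claim, a few sentences and a few extra tables. Sections 3.4 and 3.5 already provide for collecting the data, so no additional patients, visits or measurements are needed.
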